#### Overall intervention effectiveness

The first set of research questions relates to the effectiveness of the intervention as compared with the control condition from pretraining to post-training. To this end, we use multilevel models to predict intake of trained ‘increase’ and ‘decrease’ foods as a function of timepoint (3 days preintervention vs postintervention), condition (intervention vs control) and their interaction. Equivalent models test the intervention effect on approach biases towards—and craving for—the two food categories. To test to what degree the effect of the training intervention is specific to trained foods, we then use data from trained and untrained stimuli and add a variable that indicates whether a food appeared in the training or not (trained vs untrained) and all interaction terms to the model. This is followed up with tests to determine whether changes in the approach bias are mainly driven by changes in approach—or avoidance RTs. We further test the moderating role of intentions, baseline stimulus craving and person-level variables obtained from the questionnaires, as well as contingency awareness and expectancy by adding the relevant variable and its interaction terms to the equations. Finally, we examine the mediating effect of craving for changes in intake.

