So far, it has mostly been ignored that approach biases may fluctuate over time. In most studies to date, approach bias has, at least implicitly, been treated as a relatively stable, trait-like phenomenon, in line with its conceptualisation as a (stable) mental construct. Approach bias is typically measured at a single time point and then correlated with other phenomena like trait food craving,^10^ weight status,^20^ or eating disorder diagnosis.^21^ One recent study demonstrated that approach bias was independent of experimentally induced satiety, indicating stability of the bias across situations. However, participants’ desire to eat specific foods did explain variance in approach bias, implying that bias might vary across time within individuals depending on their current consumption desires.^22^ This is in line with the finding that approach bias for chocolate was positively correlated with current chocolate craving,^23–25^ craving being an experience of intense desire for a specific food which is temporally variable by definition.^26^ Other studies using a mobile version of the AAT indicated that test-retest reliability across eight measurement occasions was low while split-half reliability was high, again indicating temporal fluctuations in approach biases.^27^ This is in line with findings obtained from other indirect measures that showed modest stability over time.^28^ Such within-subject fluctuations in biases are probably not only due to random variation, as approach-avoidance biases have been shown to decrease with after-meal-satiety in normal-weight individuals, and they have been shown to change based on individuals’ current affective states.^29–33^ In combination, these results raise questions about the temporal and situational stability of approach biases.

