### Participants

Participants will be recruited via university e-mailing lists, social networks, university events and word of mouth. Participants must be between 18 years and 60 years of age, and must not be pregnant or report a diagnosis for an eating disorder. Importantly, participants must have an intention to change their eating behaviour (which they indicate on sign-up), without further specification regarding increased or decreased intake of certain foods or food categories.

To determine the required sample size, we performed a power analysis using pre-existing data from a (so far unpublished) study, where we attempted to change participants' approach-avoidance bias and analysed its change from pre-training to post-training (see online supplemental file 1 for more information). We opted to use this pre-existing data as the structure of the study is similar to the current study and the correlations and noise therein would be more likely to reflect the findings we will observe than would fully simulated data.

10.1136/bmjopen-2022-070443.supp1Supplementary data

First, group-level differences between the pre-to-post effects of sham and active training were removed such that a time-by-group effect size of 0 was achieved. A new effect size was then applied by increasing the post-treatment group mean of the active training participants by a multiple of 16 between 64 and 244, giving effect sizes around *g*=0.5. After this, participants were randomly sampled with replacement such that sample sizes between 80 and 180 in multiples of 10 were achieved. Each combination of sample size and effect size was resampled and tested 200 times. After sampling a set of participants, a multilevel analysis was performed where approach-avoidance bias scores were predicted with fixed predictors of treatment group (sham or active) and time (pretraining or post-training), as well as random effects of time grouped by participant and time grouped by stimulus. The p value of the group by time interaction was recorded. The proportion of p values below.05 was computed to determine the power at each combination of sample size and effect size.

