Based on this power analysis, we determined that a medium effect size (*g*=0.50) and a power of 0.80 would require a sample size of about 150 participants. Based on the effect size observed in that other study of *g*=0.56, 150 participants result in a power of about 0.88. A table with all power analysis outcomes is depicted in online supplemental file 2. With an estimated recruitment rate of three participants per week and allowing for recruitment difficulties slowing down the process, we expect data collection to last from November 2022 to roughly January 2024. Data collection continues until 150 participants are reached.

10.1136/bmjopen-2022-070443.supp2Supplementary data

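### The pre-to-post effectiveness test is in effect a change-score comparison; it is valid, but adjusting for the baseline already collected would be more precise, most of all for approach bias

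*Protocol article*

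**What the plan says.** The section Overall intervention effectiveness models intake of trained foods by timepoint, "condition (intervention vs control) and their interaction. Equivalent models test the intervention effect on approach biases" and craving. The treatment effect is therefore the condition-by-timepoint interaction, with condition retained as a main effect. Baseline craving appears only later, as a possible moderator.

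The sample-size text under Participants uses the same structure. Bias scores were modelled with "fixed predictors of treatment group (sham or active) and time (pretraining or post-training), as well as random effects of time grouped by participant" and by stimulus, and then: "The p value of the group by time interaction was recorded". The resulting claims are that "a power of 0.80 would require a sample size of about 150 participants" at g = 0.50, and that at g = 0.56 "150 participants result in a power of about 0.88".

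On stability over time, the introduction reports from other studies with a mobile task that "test-retest reliability across eight measurement occasions was low while split-half reliability was high". Under Ecological momentary assessment, pre and post bias each come from one session, on day 4 and day 17.

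The Data analysis plan places the exact formulas in a preregistration that is not at hand.

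**The concern.** Randomisation makes the expected baseline means of the two arms equal. A model that still estimates them separately spends information on a difference known to be zero in expectation, and the noise in that estimated difference passes into the treatment effect. If the arms happen to differ at baseline by d, the change score moves the estimated effect by -(1-rho)d; at rho 0.3 that is 70% of the imbalance, with reversed sign. Averaged over randomisations this is no bias, but it adds variance.

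The weaker the pre-post correlation, the larger the loss. The article itself describes approach bias as a measure that fluctuates between occasions, so this main outcome is where the choice of estimator matters most. At stake is precision that could be had without recruiting anyone further.

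**Working it through.** **Inputs.** From the article: two groups, 150 in total, g = 0.50 with power 0.80, g = 0.56 with power about 0.88, p below 0.05. Assumed: two-sided test, 75 per arm, complete data, equal variance at both timepoints, and rho (person-level pre-post correlation) over a range, because no value is given.

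**The plan's own figure.** The simple two-sample formula gives 2(1.960+0.842)²/0.50² = 62.8, so 63 per arm or 126 in total. At 75 per arm it gives power 0.865 (g = 0.50) and 0.929 (g = 0.56). These differ from 150, 0.80 and 0.88. That shows no error: the stated values come from resampling unpublished data with participant and stimulus effects, and cannot be rerun here. The two stated powers agree with each other, since both imply an SD about 1.09 times the one that standardises g. If g is scaled to the single-occasion SD, a change-score test with rho near 0.40 gives 0.798 and 0.879 and a total of 152. That rho is fitted, not documented.

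**Is the interaction a change score?** In one simulated data set (75 per arm, four foods, participant random intercept and time slope), the mixed-model interaction was 0.4409 with SE 0.2213. The difference in mean change was 0.4409 with SE 0.2213.

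**Variance.** With s² the person-level variance at one timepoint, the per-person variance entering the comparison is:
- change score: 2s²(1-rho)
- baseline-adjusted: s²(1-rho²)
- ratio, adjusted to change score: (1+rho)/2

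Below rho 0.5 the change score is less precise even than comparing post values alone, whose variance is s².

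**Power for approach bias, taking the stated 0.80 at 150 as given.** The noncentrality is 1.960+0.842 = 2.802. After adjustment it is 2.802/√ratio, and power is Φ(that value - 1.960). The equivalent total under the present test is 150/ratio.

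| rho | ratio | adjusted power at 150 | simulated | equivalent total, present test |
|---|---|---|---|---|
| 0.2 | 0.60 | 0.951 | 0.947 | 250 |
| 0.3 | 0.65 | 0.935 | 0.928 | 231 |
| 0.5 | 0.75 | 0.899 | 0.896 | 200 |
| 0.7 | 0.85 | 0.860 | 0.857 | 176 |

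The simulation used 75 per arm and 4,000 runs per rho; the change-score test had power 0.79 to 0.80 throughout.

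**Two traps in the remedy.**
- If timepoint and condition are both factors, deleting the condition main effect changes nothing. The software fits a condition effect at each timepoint, and the design matrix has rank 4 with or without the main effect. A numeric 0/1 post indicator is needed; the rank is then 3.
- A food-level baseline covariate alone need not deliver the ratio above. In simulations with four foods and food noise independent over time, the variance ratio to the change score was about 0.71 at rho 0.3, 0.91 at 0.5 and 1.2 to 1.3 at 0.7, the last being worse than no adjustment. The person-mean baseline must enter as well. These ratios depend on the food noise assumed.

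**The case against.** The strongest reply is that nothing here is wrong. A condition-by-timepoint interaction in a multilevel model is common and unbiased, and 150 was derived from that very test, so the stated power already carries the baseline noise. This stands. A reader might infer that the trial is underpowered, or that a null result would be an artefact of the estimator; the article supports neither.

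A second reply concerns scope, and it also stands. The low-reliability statement and the power calculation both concern approach bias, and the former comes from other studies. A reader might carry the power figures over to intake and craving, but the article states no power and no pre-post correlation for them. Both are reported over several days, may correlate more strongly, and would then gain less.

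A third reply is that the preregistered formulas are not shown and might already adjust for baseline. That cannot be excluded, although the article's stated terms and its power model agree.

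Finally, a common-baseline model relies on equal expected baselines among those analysed, and the Data exclusion section removes some participants and sessions after randomisation. That is a small weakness: baseline measurement precedes training, and the participants removed did no intervention-phase session in either arm.

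**Conclusion.** The point holds as a recommendation on efficiency, not as an error. As stated, the main pre-post test is a change-score contrast, and for any rho below 1 baseline adjustment is at least as precise in large samples. For approach bias, at rho 0.2 to 0.7, power at 150 would rise from the stated 0.80 to between 0.95 and 0.86. This rests on an assumed rho, a two-sided test, 75 per arm and complete data. Missing sessions and stimulus effects make the ratio approximate. For intake and craving only the direction can be stated.

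**What to change.** In the main pre-post effectiveness models, do one of the following:

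- **(a) Common baseline mean.** Code timepoint as a numeric indicator, 0 before and 1 after. Include only post and post × condition as fixed effects, with a correlated participant intercept and post slope.
- **(b) Baseline covariates.** Model the post values on condition, with both the participant's mean baseline and each food's deviation from that mean as covariates.

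Apply the choice to bias, intake and craving, and state it in the preregistration before the data are analysed by arm. If the preregistered formulas already do this, the article only needs to say so.

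The cost is a note to the preregistration, matching constraints in the trained/untrained and moderator models, and a sentence stating the reliance on equal expected baselines after the exclusions. No new data are needed, and the target of 150 can stay.

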Have you spent more money today than you wanted to?	X	X	X	X
Have you felt impatient today?	X	X	X	X
Have you made a spontaneous decision today?	X	X	X	X
How strong has your craving for this food been *since the midday questionnaire*?*			X	
How much of this food have you eaten *since the midday questionnaire*?*			X	
How much do you expect that this task will help you reach your dietary goals?†	X†			
Throughout the whole study, how often did you push this food away from yourself?*				X
Please indicate the day your last period started.				X

All items are answered on a slider from 0 to 100 unless indicated differently in parentheses. Midday prompts remain the same across the entire study duration. Evening prompts differ depending on the study phase as indicated:.

*These items are asked alongside a food image and are repeated for each image (six ‘increase-food‘ and six ‘decrease-food’ images).

†This item is only asked after the first and the last AAT session (days 5 and 15).

AAT, Approach Avoidance Task; EMA, ecological momentary assessment.

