**Figure 3 F3:**
[figure not shown]
Time schedule of the whole study period. AAI, approach-avoidance intervention; AAT, Approach Avoidance Task; EMA, ecological momentary assessment.

In addition, on day 6 and day 16 (the first day and the last day including an AAT/AAI session), participants further indicate their expectancy of how much the task will help them reach their dietary goals. Four weeks after the end of the initial 20-day EMA period, participants receive one additional EMA questionnaire and a measurement AAT in the evening. After performing this final AAT, participants indicate how often they believed they pushed or pulled each of their ‘decrease-foods’ and ‘increase-foods’.

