#### Procedure

The procedure for study participation is as follows: after interested participants contact the study team, they receive an individual participant code and a web link to the baseline questionnaire. At this point, an R-script (The function *sample* randomly outputs the number ‘1’ or ‘2’ which correspond to the conditions.) randomises participants to either the intervention or control group with the condition unknown to the study team. After a set-up call with a member of the research team within a few days of filling out the questionnaires, participants start receiving EMA prompts and AAT as described above. Figure 3 shows the timeline of the whole study. Throughout the study period, participants can contact study personnel who also monitor compliance to the EMA and AAT schedule and contact participants in case of low compliance: participants receive an email if they miss more than one of the first three AAT/AAI sessions.

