#### Secondary outcomes

Dietary intentions are measured according to the outlined EMA schedule.

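### Contingency awareness and expectancy are tested as moderators although both are recorded only after arm-specific training has begun, so their interactions with condition are not baseline effect modification

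*Protocol article*

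**What the plan says.** The subsection on overall intervention effectiveness models intake, craving and approach bias by timepoint, condition and their interaction. It then adds moderators: "We further test the moderating role of intentions, baseline stimulus craving and person-level variables obtained from the questionnaires", and continues "as well as contingency awareness and expectancy by adding the relevant variable and its interaction terms to the equations". Craving is given as a baseline value. No time window is given for intentions, awareness or expectancy.

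The timing of each variable is found elsewhere in the article:

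- **Randomisation** takes place when the participant code and the link to the baseline questionnaire are issued (Procedure). A script "randomises participants to either the intervention or control group with the condition unknown to the study team".
- **Awareness** is asked at the follow-up, four weeks after the 20-day assessment period: "After performing this final AAT, participants indicate how often they believed they pushed or pulled each" of their foods. Table 1 lists the item in the follow-up column only: "Throughout the whole study, how often did you push this food away from yourself".
- **Expectancy** carries a footnote in Table 1: "This item is only asked after the first and the last AAT session", with days 5 and 15 named. The text after Figure 3 gives days 6 and 16.
- **Intentions** are collected before, during and after training, and are also the secondary outcome: "Dietary intentions are measured according to the outlined EMA schedule".

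**The concern.** A condition-by-moderator interaction answers the question of who benefits only if the arm cannot have changed the moderator. If the arm can change it, participants with the same value in the two arms are not comparable, and the interaction mixes effect modification with selection.

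Awareness is the clearer case. It is recorded after the training and after the outcomes it is meant to moderate, and only in participants who reach follow-up. The item asks how often each food was pushed, and the active arm really did push its trained decrease-foods more often. The same rating can therefore be accurate recall in one arm and an error in the other. A participant whose eating changed may also recall or report more pushing.

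What is at stake is the interpretation of the mechanism. The Introduction says awareness could strengthen the intervention, and gives this as a reason for the relevant-feature task and for tracking awareness closely. A positive interaction would be easy to read as support for that idea.

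**Working it through.** **1. Trial counts (Approach-Avoidance Task).** Training session: 4 blocks × 16 = 64 trials, plus 4 × 4 = 16 practice = 80. Measurement session: 4 blocks × 24 = 96, plus 16 practice = 112. Both agree with the article. Blocks alternate, so two of the four are avoid-food blocks. Practice trials are left out below.

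**2. Pushes per trained food.** Assumption: each 16-trial training block has 8 food and 8 object trials.

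- Measurement tasks (pre, post, follow-up): each food appears once per block, so 2 pushes and 2 pulls per session. Over three sessions this gives 6 pushes and 6 pulls.
- Active training: 8 food trials in an avoid-food block are spread over 4 decrease-foods, so each appears twice. Two such blocks give 4 pushes and 0 pulls per session.
- Sham training: 8 food trials are spread over 8 foods, so each appears once per block. This gives 2 pushes and 2 pulls per session.

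With s training sessions each trained food is shown 12 + 4s times. The push share is:

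| Trained food | Formula | s = 6 | s = 1 |
|---|---|---|---|
| Active, decrease | (6 + 4s)/(12 + 4s) | 30/36 = 83.3% | 10/16 = 62.5% |
| Active, increase | 6/(12 + 4s) | 6/36 = 16.7% | 6/16 = 37.5% |
| Sham, either | (6 + 2s)/(12 + 4s) | 18/36 = 50% | 8/16 = 50% |

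Untrained foods are pushed 6/12 = 50% in both arms.

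**3. Order of measurement.** Training falls within days 5 to 16, the post-intervention measures run from day 17 to day 20, and awareness comes four weeks later. Expectancy comes after a session by the footnote. No awareness value precedes the arm-specific task and, by the footnote, no expectancy value does.

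**4. Can an interaction appear without a true modifier?** This is an illustration with assumed inputs. T is the arm (75 per arm, N = 150) and U is a standard normal trait.

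- Outcome change: Y = 0.5T + bU + √(1 − b²)·e₁. The effect is 0.5 SD for everyone.
- Awareness: A = T(gap + 20U) + 20e₂, in points. The trait raises awareness in the active arm only.
- Within the active arm the slope of Y on A is 20b/(20² + 20²) = b/40 per point; within sham it is 0. With b = 0.3 the slopes differ by 0.0075 per point although the treatment effect is constant.

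Share of 1,000 runs per setting in which the T × A term has p < 0.05:

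| Mean perceived gap | b = 0 | b = 0.3 | b = 0.5 |
|---|---|---|---|
| 20 points | 4.7% | 18.1% | 42.2% |
| 40 points | 5.8% | 19.7% | 43.3% |
| 66.7 points | 6.6% | 18.4% | 45.6% |

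The excess comes from the shared trait, b, and hardly depends on the size of the gap between arms.

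**The case against.** - **The exact formulas are in a preregistration that is not shown.** This is true, and the preregistration may define the awareness score and the window for intentions. It cannot alter when awareness is collected, and the article itself assigns the moderator role.
- **A reader might infer that intentions are disqualified too, as a secondary outcome measured after randomisation.** The article does not support this. Intentions on days 1 to 3, and on day 4 where both arms do the same measurement task, precede any difference between arms in a double-blind trial. They are legitimate moderators. Only values from day 5 on would be a problem, and the article does not say that those are used.
- **A reader might infer that anything measured after randomisation is ruled out.** That would also remove the baseline questionnaires, which follow randomisation. Order alone disqualifies nothing; what counts is whether the arm could have changed the value.
- **A reader might infer that awareness is merely a stand-in for arm.** This depends on adherence, recall and scoring. With raw ratings, unbiased recall and an assumed rating SD, r = h/√(h² + SD²), where h is half the gap between arms. For six sessions (h = 16.7) r is 0.74 at SD 15 and 0.49 at SD 30. For one session (h = 6.25) it is 0.38 and 0.20. The documents give no rating SD and no scoring rule, so the strength of the link is unknown.
- **The spurious interaction is assumed.** With no shared trait, rejection stays at about 5 to 7%. The illustration shows that the problem can arise; it does not estimate how large it is here.
- **Expectancy might be asked before the first session.** Table 1 puts the item in the midday column, and training follows the midday prompt. If so, the first reading would be admissible. The footnote says otherwise, so the point on expectancy rests on the footnote.

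**Conclusion.** The point holds for contingency awareness without reservation on timing, and for expectancy as the Table 1 footnote describes it. Interactions of these variables with condition cannot be read as baseline effect modification. For trained foods the true push share differs by arm: 83.3% against 50% for decrease-foods with full adherence and 62.5% against 50% with one session, given equal numbers of food and object trials per training block. Perceived frequency may follow these shares less closely. A false interaction is possible if a trait drives both awareness and outcome change; its likelihood cannot be derived from the article.

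A reader might infer that the randomised comparison as a whole is compromised. It is not. The condition-by-timepoint tests on intake, craving and approach bias do not use these variables. The weakness is confined to the add-on models and to what is concluded from them.

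**What to change.** 1. Limit moderator claims to variables the arm cannot have changed: questionnaire traits, pre-phase craving, and intentions from days 1 to 4, with that window stated.
2. Analyse awareness and expectancy as outcomes compared between arms, as mediators with the assumptions written down, or as associations within an arm labelled exploratory.
3. State how awareness is scored. Scoring it against the food's true push share in that arm removes the built-in difference between arms, but it does not turn awareness into a pre-treatment variable.
4. Reconcile the expectancy timing: days 5 and 15 in the Table 1 footnote against days 6 and 16 in the text, and the midday column against a question asked after the session.

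No new data are needed, and the work is rewording of additional analyses. The cost is that the claim of moderation by awareness or expectancy is given up.
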